## 4 Treatment Administration and Patient Management

The goal of study treatment is to reach and maintain an HbA1c level  $\leq 6\%$ .

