#### 4.2.2 Hypoglycemia

If a patient who is not receiving insulin has a severe hypoglycemic event as defined by the need to be treated with glucagon, the need for a third party to resolve a hypoglycemic episode, or loss of consciousness or seizure, then study medications are adjusted downward. If after one month there are no additional hypoglycemic events and if HbA1c values rise to > 6%, the dose of study medications is returned to the previous dose. If a second episode of severe hypoglycemia occurs, the dose is decreased until the end of the trial. If more than two severe hypoglycemic events occur in the same patient in the absence of insulin, then the patient is unmasked and study medications are adjusted downward until hypoglycemia is resolved.

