#### 4.7 Add-on Insulin Therapy

- *Failure to maintain adequate metabolic control:* If HbA1c  $\geq$  8.0%, therapy is re-invigorated by more frequent telephone contact and visits. If HbA1c remains  $\geq$  8% throughout the next six months, then the patient is classified as failing to maintain

adequate metabolic control and *if* the participant's fasting blood glucose values are not in target then add-on therapy with insulin is initiated.

- *Outcome assessments before the initiation of add-on insulin therapy:* Before starting insulin treatment, participants undergo a comprehensive outcomes assessment unless this has been completed within the past three months.
- *Add-on insulin treatment regimen:* Patients who meet criteria for add-on insulin therapy continue to take the study drug metformin but discontinue the study drug rosiglitazone. The patients and clinicians remain masked to the treatment assignment but are unmasked to HbA1c. Initial insulin treatment is glargine insulin, 0.2 units per kilogram given in the evening. The dose is increased up to 1.0 U/kg/day (to a maximum of 100 units), until fasting blood glucose (FBG) values between 70-150 mg/dL are achieved.  
Add-on glargine insulin therapy is considered unsuccessful if (1) 1.0 U/kg/day (to a maximum of 100 units) does not bring FBG to target within 1 month or (2) HbA1c > 8% at 3 months or (3) HbA1c > 7% at 6 months. At that point, insulin therapy—including adding rapid, short, or intermediate acting insulin—is provided at the clinician's discretion.
- *Self-monitoring of blood glucose (SMBG):* During insulin therapy, patients are asked to monitor blood glucose levels at least four times a day. Target fasting glucose and pre-meal glucose is 70-150 mg/dL and the target peak postprandial glucose is  $\leq 200$  mg/dL.

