- *Gastrointestinal (GI) symptoms* are a common occurrence with metformin. However, these symptoms more commonly occur early in the course of treatment. Since all eligible participants are placed on the maximal tolerated metformin dose (between 500 mg bid and 1000 mg bid) during the run-in period, few additional gastrointestinal side effects are anticipated in these patients. If GI side effects develop and are mild, the patient is encouraged to remain on the study medication. If GI side effects are moderate or difficult to tolerate, metformin (but not rosiglitazone) is reduced to the next lowest dose (for example, 1000 mg bid to 1000 mg + 500 mg; 1000 mg + 500 mg to 500 mg bid; etc.). If symptoms persist, metformin is reduced to the next step. If GI symptoms resolve, metformin is re-escalated by 500 mg per day each week until reaching the previously tolerated dose. If symptoms persist on a dose of metformin that is only 500 mg bid, study medication is discontinued.
- *Edema* is considered clinically significant if there is pitting edema above the patient's ankle. A thorough evaluation of potential causes is conducted, and the dose of study medication is reduced (if necessary, medication is stopped). As with any serious adverse event, if the patient is experiencing severe symptoms along with clinically significant edema, the SAE should be reported according to study procedures.
- *Severe hypoglycemia* is defined by the need to be treated with glucagon, the need for a third party to resolve a hypoglycemic episode, or loss of consciousness or seizure. Study medications are adjusted downward. If after one month there are no additional hypoglycemic events and if HbA1c values rise > 6%, then the dose of study medications is returned to the previous dose. In case of a second episode of severe hypoglycemia, the dose is decreased until the end of the trial. If more than two severe hypoglycemic events occur in the same patient in the absence of insulin, then the patient is unmasked and study medications are adjusted downward until hypoglycemia is resolved.  
If severe hypoglycemia occurs while on insulin, the insulin dose is reduced by 20%. After one month, if there are not additional hypoglycemic events or if HbA1c values rise to > 6%, then the dose is increased by 10% a month until it returns to the previous level. If a second episode of severe hypoglycemia occurs, insulin dosage adjustment is performed at the discretion of the investigator.

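### Protocol 6.2.4 restores insulin after severe hypoglycemia on an *or* where the parallel study-drug rule has *and*, and does not say which further hypoglycemic events count

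*Protocol*

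**What the plan says.** Section 6.2.4 (Procedures to Minimize Risks) has one bullet on severe hypoglycemia. It defines the term by use of glucagon, third-party help, or loss of consciousness or seizure, and then gives two dose rules.

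- **Study medication.** The dose is lowered. It goes back to the previous dose on this condition: "If after one month there are no additional hypoglycemic events and if HbA1c values rise > 6" percent. Section 4.2.2 (Hypoglycemia) says the same: "If after one month there are no additional hypoglycemic events and if HbA1c values rise to > 6" percent.
- **Insulin.** The dose is cut by 20%. The rule that applies from one month onward is: "if there are not additional hypoglycemic events or if HbA1c values rise to > 6%, then the dose is increased". The increase comes in monthly steps of 10% and stops at the previous level. A second severe episode has its own sentence: "If a second episode of severe hypoglycemia occurs, insulin dosage adjustment is performed at the discretion of the investigator".

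Three other statements bear on the rule. Section 4 sets the HbA1c target at 6% or below ("The goal of study treatment is to reach and maintain an HbA1c level"). Section 4.7 (Add-on Insulin Therapy) starts glargine at 0.2 U/kg and fixes its range: "The dose is increased up to 1.0 U/kg/day (to a maximum of 100 units"). The same section sets a fasting and pre-meal glucose target of 70 to 150 mg/dL and adds: "During insulin therapy, patients are asked to monitor blood glucose levels at least four times a day".

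**The concern.** The two rules share the one-month wait, the 6% threshold and the condition on further events. Only the connective differs, and no reason is given. With *and*, both conditions must favour a dose increase. With *or*, one is enough, so a condition meant as protection can be bypassed.

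The trigger also leaves a term open. The bullet is about severe hypoglycemia, and it writes *severe* when it speaks of a second episode. The condition for raising insulin speaks of hypoglycemic events without that word. A site must decide for itself whether a mild low counts.

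What is at stake is the safety of young patients who have just had a severe episode. The rule takes insulin back toward the dose at which that episode happened. The instruction should not be automatic where lows are continuing, or where HbA1c is already at goal.

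**Working it through.** The protocol gives no figure to reproduce here. The check has two parts: comparing the rules case by case, and working out how much insulin is restored.

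**1. The two rules side by side** (6.2.4 and 4.2.2), treating *rise to above 6%* simply as HbA1c above 6%:

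| Further events | HbA1c above 6% | Study-drug rule (*and*) | Insulin rule (*or*) |
|---|---|---|---|
| No | Yes | Restore | Raise |
| No | No | Hold | Raise |
| Yes | Yes | Hold | Raise |
| Yes | No | Hold | Hold |

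The study-drug rule restores the dose in 1 of 4 cases. The insulin rule raises it in 3 of 4.

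**2. The effect of each reading of *further events***

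- *Any hypoglycemia.* In the third row, HbA1c alone triggers the increases. If the further event is severe, the next sentence hands the decision to the investigator. The automatic increase therefore remains for non-severe lows.
- *Severe episodes only.* Any further event is then a second severe episode, so the third and fourth rows go to the investigator. The first and second rows both lead to an increase, whatever the HbA1c. The HbA1c clause never changes the instruction, and the second row raises insulin at 6% or below, which is the goal in section 4.

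Neither reading gives a rule in which both conditions do their work. With *and*, both do.

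**3. How often HbA1c would exceed 6%.** Under 4.7, add-on insulin follows HbA1c of 8% or more throughout six months. Glargine counts as unsuccessful only above 8% at 3 months or above 7% at 6 months. Values above 6% are therefore likely to be common on add-on insulin. The protocol gives no rate of severe hypoglycemia on insulin, so the number of patients affected cannot be derived.

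**4. Insulin restored per patient** (20% cut and 10% steps from 6.2.4; dose range from 4.7)

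- After the cut: 1.00 × 0.80 = 0.80 of the previous dose.
- Steps of 10% of the original dose: 0.80 + 0.10 = 0.90; 0.90 + 0.10 = 1.00. Two steps.
- Steps of 10% of the current dose: 0.80 × 1.10 = 0.88; 0.88 × 1.10 = 0.968; 0.968 × 1.10 = 1.065, capped at 1.00. Three steps.

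| Dose before the episode | After the cut | Amount restored |
|---|---|---|
| 0.2 U/kg/day (starting dose) | 0.16 | 0.04 U/kg/day |
| 1.0 U/kg/day | 0.8 | 0.2 U/kg/day |
| 100 units/day (glargine maximum) | 80 | 20 units/day |

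If the first step is taken at one month (an assumption), the previous dose is back 2 to 3 months after the episode. The 100-unit ceiling applies to add-on glargine. Total insulin can be higher once other insulins are added.

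**The case against.** A reader might infer that the protocol plainly orders more insulin for patients who are still having lows, and that the *or* is a proven slip. The documents do not support that, for four reasons.

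- The bullet is headed and defined by severe hypoglycemia, so the further events can reasonably be read as severe ones. The protocol defines no non-severe event.
- The HbA1c condition speaks of a rise to above 6%. A patient who was above 6% all along has not clearly met it.
- The HbA1c branch has limited reach. During temporary insulin, HbA1c outcome measurement stops except in pregnancy and nursing (4.7). HbA1c is scheduled every 2 months in year 1 and quarterly afterwards (5.1), so a value will often be missing at one month.
- The insulin rule differs from the study-drug rule in other ways: a fixed cut, gradual steps, and discretion after a second severe episode. Patients on add-on insulin have had poor control and may need the dose back. A different connective could be intended.

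Harm is also bounded. The increase stops at the previous dose. Section 4.7 sets a lower glucose limit of 70 mg/dL and asks for testing at least four times a day. Once glargine is unsuccessful, further insulin therapy "is provided at the clinician's discretion", and the treatment team has similar latitude during temporary insulin. Severe hypoglycemia is reported as a serious adverse event (6.4.2).

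All of this stands, and it lowers the weight of the point without removing it. The severe-only reading leaves the HbA1c clause idle and still raises insulin at goal, although raising insulin after an event-free month can be defended clinically. No latitude is stated for a patient still in the glargine titration phase, where 6.2.4 is the specific instruction.

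**Conclusion.** The point holds as a minor correction of safety wording. The insulin rule in 6.2.4 has an unexplained *or* and an undefined trigger, and it works poorly on either reading. Which reading was intended, and whether the difference was deliberate, cannot be settled from the protocol.

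The dose effect is limited to reversing the 20% cut in two or three monthly steps. The dose figures rest on the glargine range in 4.7 and on a first step at one month.

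A reader might also infer that the trial's results are at risk. They are not: the rule concerns dose management on insulin and does not enter the sample size, the type I error or the primary analysis.

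**What to change.** Replace the insulin re-escalation sentence in 6.2.4 with wording to this effect:

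> One month after the cut, raise insulin by 10% a month, up to the dose before the episode, only if (a) no further hypoglycemia has occurred, whether severe, symptomatic, or a measured glucose below 70 mg/dL (the lower limit of the target in section 4.7), and (b) HbA1c is above 6%. In every other case the investigator decides on the insulin dose.

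Keep the sentence on a second severe episode. The definition in (a) is needed: with *and* alone, a site that counts only severe episodes would still raise insulin automatically through mild lows. Writing that HbA1c *is* above 6% removes the doubt about a rise from a lower value. The closing sentence covers a poorly controlled patient with a mild low, who is then not held at the reduced dose indefinitely, and a patient with no HbA1c at one month.

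The cost is one amended sentence, adopted under section 9.8 (two-thirds approval by the voting members of the Treatment Protocol Committee and resubmission to the IRB), and a note to sites. The downside is a slightly slower return to the previous insulin dose in some patients.

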### 6.3 Unmasking

Unblinded treatment assignments are held by the coordinating center, the Drug Distribution Center, and, if used, the clinical center central pharmacy.

Each TODAY participant is given a card with clear instructions how to contact a TODAY study representative. The TODAY clinical center nurse coordinator is the primary contact during working hours, the TODAY clinical center on-call physician is the primary contact after clinic hours, and the TODAY Drug Distribution Center is the backup contact. In case of emergency, the patient hands the card to the emergency health care provider who makes the contact as needed. The TODAY clinical center nurse or physician contacts the study chair (or the medical consultant, if the study chair is unavailable) in case of an emergency, illness, or condition that may warrant unmasking. The decision to unmask is made by the study chair (or the medical consultant, in the absence of the study chair).

Every attempt is made to avoid unnecessary unmasking.

### 6.4 Adverse Event and Serious Adverse Event Reporting

#### 6.4.1 Purpose of Adverse Event Reporting

The reporting of adverse events experienced by study participants meets three important purposes:

1. It identifies the frequency and severity of known and unanticipated side effects of the study interventions (metformin, rosiglitazone, TLP) within each study arm of the trial.

2. It provides the mechanism for reporting the occurrence and severity of adverse events to the study group, the NIH, the FDA, and the pharmaceutical company(s) providing the medications.
3. It fulfills the FDA requirements for reporting adverse reactions to medications.

The timely and complete reporting of adverse events is a critical requirement in the conduct of this trial.

#### 6.4.2 Definitions of Adverse Events

- *Adverse Event (AE)*: Any unfavorable and unintended change in the structure, function or chemistry of the body experienced by a study participant during the study regardless of the relationship of this change to administration of study intervention or participation in the study. Adverse events include symptoms and changes in laboratory data that are not specifically part of the primary or secondary outcomes of the trial. AEs are reported only at scheduled study visits unless they meet the criteria for being serious.
- *Serious Adverse Event (SAE)*: Events are divided into those that are serious (SAEs) and those that are not serious (AEs). The distinction between an SAE and an AE is a regulatory definition established by the FDA, not a clinical definition. The definition of SAE is not always related to clinical severity of the event. An AE is considered serious (SAE) when it satisfies any one of the following criteria:
  - a. The event results in an inpatient hospitalization (any overnight stay associated with an admission).
  - b. The event results in the prolongation of a hospital stay.
  - c. The event results in permanent or severe disability.
  - d. The event results in death.
  - e. A pregnancy results in a congenital anomaly.
  - f. The event results from an overdose (either accidental or experimental) of the study medication.
  - g. The event is life-threatening.
  - h. Treatment is required to prevent a serious event.
  - i. The patient experiences a bout of lactic acidosis.
  - j. An episode of severe hypoglycemia occurs.

#### 6.4.3 Non-serious Adverse Events

It is essential that AEs be ascertained in an unbiased manner using standard questions that are identical and identically administered to patients in all three treatment arms. Therefore, AEs are reported on a standard form that is completed by the study staff at each regular follow-up visit. AEs are ascertained by asking targeted questions relating to specific events of import in diabetic patients on any of the study treatment arms. AEs also include any significantly abnormal physical finding identified on examination and any significantly abnormal laboratory result obtained on the patient between visits or at the time of the visit. Questions answered YES and any new abnormal physical findings are pursued by the study staff in order to determine the seriousness of the event and the need for further evaluation, follow-up, or referral. Adverse events reported or ascertained between clinic visits are captured and reported at the time of the next scheduled visit.

Pre-existing conditions (that is, conditions present prior to randomization) are not considered or recorded as AEs or SAEs unless the condition worsens in intensity or frequency after randomization. Likewise, continuing adverse events are not reported as AEs at subsequent visits unless they increase in severity or frequency between the visits, they result in criteria for an SAE, and/or they resolve between visits.

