- Urine ketones are measured as indicated if BG > 300 mg/dL.
- Serum creatinine is used to calculate creatinine clearance.
- If transaminases > 1.5 ULN, safety protocol is followed.
- Other anthropometric measurements are waist circumference and abdominal height.
- Screening lipid values are LDL and TG for determining eligibility. Other lipid assays include free fatty acids, lipoprotein subclass levels, average LDL particle density, and total ApoB levels.
- A comprehensive physical exam including Tanner stage and evaluation of acanthosis nigricans is performed at screening, baseline, all annual visits, and outcome. Otherwise a targeted physical exam is performed (every 2 months in year 1 follow-up and then quarterly).
- The FFQ is used for nutrition, 3-day PDPAR and 7-day recorded accelerometer for physical activity, and PWC 170 for fitness.
- The psychosocial and quality of life battery includes CDI, BDI, EDEQ (and QEWP-R if participant has high score on the EDEQ), PEDS QL, and HUI-2.
- Cardiovascular risk factors include measurement of fibrinogen, c-reactive protein, homocysteine (vitamin B-12 will be obtained to assess homocysteine), plasminogen activator inhibitor-1, interleukin-6. Pro-inflammatory and hemostasis markers are assayed at baseline, 6 months, 12 months, and end of study; blood from other draws is stored.
- Participants are asked about adverse events (AE) at clinic visits, but AE and SAE (serious adverse events) may be reported by the patient at any time.
- Data collected from the biological parent at baseline are height, weight, BDI, and EDEQ (and QEWP-R depending on EDEQ high score).
- Survey data include BDI, EDEQ (and QEWP-R depending on EDEQ high score), PEDS QL (adult proxy) and CHQ (P28).
- Data are collected every 2 months during the first year and quarterly thereafter from clinic staff on time spent for patient treatment. Logbook data are collected from clinic

staff every four months to further assess time spent providing treatment. Data are collected from patients and families regarding time and resource use related to treatment at baseline, 6 months, annually, primary endpoint, and at study closeout.

(p) The last HbA1c value during run-in is considered the baseline HbA1c.

(q) A sample of blood for DNA may be collected any one time after randomization.

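### Section 6.4.3 describes only targeted questions for eliciting symptoms and states no open question, so unlisted, non-serious, purely symptomatic harms rest largely on spontaneous report

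*Protocol*

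**What the plan says.** Three parts of protocol section 6.4 bear on this.

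- **Purpose (6.4.1).** The first of three listed purposes reads: "It identifies the frequency and severity of known and unanticipated side effects of the study interventions". It applies within each study arm.
- **Definition (6.4.2).** An AE is "Any unfavorable and unintended change in the structure, function or chemistry of the body experienced by a study participant during the study", whether or not it is related to the intervention. Symptoms are included.
- **Method (6.4.3).** Unbiased ascertainment by standard questions, the same in all three arms, is called essential. The questioning method is then given: "AEs are ascertained by asking targeted questions relating to specific events of import in diabetic patients on any of the study treatment arms".

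Section 6.4.3 adds further routes. On findings and tests it says: "AEs also include any significantly abnormal physical finding identified on examination and any significantly abnormal laboratory result obtained on the patient between visits". Results from the visit itself count too. On follow-up it says: "Questions answered YES and any new abnormal physical findings are pursued by the study staff". For the time between visits it says: "Adverse events reported or ascertained between clinic visits are captured and reported at the time of the next scheduled visit".

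Elsewhere, a note to the section 5.1 table says that "Participants are asked about adverse events (AE) at clinic visits" and may report AEs and SAEs at any time. The table schedules an interim history, concomitant medications and a physical examination at every follow-up visit. Section 6.4.4 has participants contact the clinic with any event that meets the SAE criteria.

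**The concern.** The purpose and the definition are open, but the questioning method is closed. An unanticipated symptom is unlikely to be on a list of events already judged important, so the described questions do not reach it. Its recorded frequency then depends on whether the participant mentions it.

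Two things are at stake. The first is under-counting of unlisted symptoms in every arm. The second is comparability. The standard of identical questioning is met for listed events but not for unlisted ones, and the opportunity to mention a symptom is not equal across arms.

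This matters more here than in a well-studied setting. Section 1.3.1 says the available agents have not been adequately evaluated in pediatric patients, section 1.3.4 mentions a single ongoing youth trial of rosiglitazone, and comparing safety across arms is the first secondary aim in section 1.1.

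**Working it through.** The plan gives no figure on this point, so there is nothing of its own to reproduce. The check is to follow a harm through each route that the protocol describes.

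**Step 1: which unlisted harms do the other routes reach?**

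| Route | Where | Reaches | Does not secure |
|---|---|---|---|
| Abnormal examination finding | 6.4.3; notes to 5.1 | Unlisted harms with a physical sign | Symptoms without a sign; between comprehensive examinations the examination is a targeted one |
| Abnormal laboratory result | 6.4.3; 6.2.2 | Unlisted harms that alter a measured test | Symptoms with no trace in the tests scheduled |
| SAE criteria | 6.4.2; 6.4.4 | Serious events of any kind | Non-serious events, by definition |
| Interim history, concomitant medications | table in 5.1 | Possibly health problems since the last visit | Content not defined; no stated link to the AE form |
| General AE inquiry at visits | notes to 5.1 | Possibly anything | Wording not given; 6.4.3 is the section that specifies the questions |
| Reports between visits | 6.4.3; notes to 5.1 | Anything mentioned or ascertained | Depends largely on spontaneous mention |

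What is left is a narrow class: non-serious, purely symptomatic events that are not on the list.

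**Step 2: is the chance to volunteer equal across arms?** All arms have visits every two months in year 1, which is 12 / 2 = 6. Section 4.4.4 adds, for the lifestyle arm only, weekly sessions in months 1-6 (about 26 weeks, so about 26 sessions) and bi-weekly sessions in months 7-12. Read as every two weeks, these are about 26 / 2 = 13, or 26 + 13 = 39 extra contacts in year 1. Since events reported between visits are recorded, extra contact can become extra recorded AEs. The protocol does not say whether lifestyle staff pass such reports on. The two arms without the lifestyle programme share one visit schedule and are masked (section 4.3), so this mechanism concerns the comparisons with the lifestyle arm.

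**Step 3: illustration only.** The inputs are 250 per arm (section 2.1) and a two-sided level of 0.05. All incidences and volunteered shares are assumptions. The statistic is z = |p1 - p2| / sqrt(2p(1 - p)/250), where p1 and p2 are the observed proportions and p is the pooled proportion. A difference is declared if z > 1.96. Power is the exact sum over two binomials with n = 250 and success probability equal to true incidence × share captured.

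| True incidence | 100% captured | 50% | 25% | 10% |
|---|---|---|---|---|
| 3% v 9% | 82.6% | 52.1% | 26.2% | 9.3% |
| 5% v 12% | 81.5% | 49.8% | 26.4% | 11.5% |

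For unequal reporting, take a true incidence of 10% in both arms, with 25% of cases volunteered in one and 50% in the other. The recorded rates are 10% × 0.25 = 2.5% and 10% × 0.50 = 5.0%. The same test then declares a difference 31% of the time although none exists. With 25% in both arms it does so 4.9% of the time.

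The 100% column is an upper bound that one open question would not reach, because an answer still needs recall and mention.

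**The case against.** A reader might infer from section 6.4.3 that AEs are elicited only by targeted questions and that any new harm is caught only if volunteered. The documents do not support that. The sentence after the targeted-question rule counts any significantly abnormal examination finding or laboratory result, neither tied to a list. Serious events follow outcome criteria, an interim history is taken at every follow-up visit, and participants are asked about AEs at clinic visits. Nor is the stated purpose to find unanticipated effects alone, since known effects come under it too. All of this stands and limits the point to the narrow class above.

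It is also fair that neither the AE form nor the manual of procedures is shown. The form may already carry an item for other events. This stands as well: the point concerns what the protocol states and does not show that the trial failed to ask.

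Targeted questions are a reasoned choice, because standard questions make expected events comparable. That argues for keeping them but does not explain how unlisted symptoms are to be counted.

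Finally, the power figures do not measure the defect. Their incidences and volunteered shares are assumed, full capture is unrealistic, and the documents describe no planned test of a single unlisted event. They should not be used to grade the point.

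**Conclusion.** The point holds in a limited form. As written, section 6.4.3 fixes a closed questioning method under an open definition and a purpose that includes unanticipated side effects. Several routes catch part of what the questions miss. For unlisted, non-serious, purely symptomatic events no route is stated that asks every participant in the same way. Their counts would rest largely on spontaneous report, and may differ between the lifestyle arm and the other two.

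The size cannot be stated from the documents, which give no volunteering rate and no incidence for such events. The direction is under-counting overall. A difference in reporting by arm is possible but not shown. The conclusion assumes that the standard form follows section 6.4.3 as written; if it already has an open item, only the wording of the section needs correcting. The change is worth making because it is cheap and serves the protocol's own stated aim. The power illustration does not carry that conclusion.

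**What to change.** In section 6.4.3, add to the standard AE form one open, non-leading question in fixed wording, for example whether the participant has had any other health problem since the last visit. Ask it at the same scheduled visits in all three arms. Code the answers and tabulate them by arm separately from the targeted items, so that elicited and open-ended rates are not mixed. If the form already has such an item, say so in section 6.4.3.

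The cost is one form item, coding of free text and more minor events to process. It needs no extra visit. The question will not capture every case, but it gives each participant the same prompt at the same times.
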